##### Parameters of gait kinematics

The maximum knee joint angle of the step phase, time parameters (including total support time and step frequency), and distance parameters (including step length, step speed, stride length and variation coefficient, etc.). The kinematics parameters of gait will be observed through three-dimensional gait analysis. A gait analyzer (MA10 System, GYENNO, Shenzhen, China) will be used to analyze the gait kinematics parameters of the two groups.

### Sample size calculation

The sample size calculations are based on the primary outcome measure, the TUGT scale [35]. It was estimated that a sample of 28 participants (14 per group) would provide 80% power (*α* = 0.05, *β* = 0.2) to detect a difference between group means of 3.16. A difference of 3.16 points on the TUGT scale is regarded as minimum detectible change [36] using the program PASS, which takes into account the number of sample groups and the number of evaluation measures. To reach this total number of individuals, at least 36 individuals must be recruited, allowing a dropout rate of 20%.

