### Randomization and blinding

The eligible participants based on the inclusion and exclusion criteria will be randomly allocated in a 1:1 ratio to either the VR training group and the non-VR training group. The attending physician will obtain the informed consent and refer the participants to the study coordinator after their baseline information has been assessed. The participants will be randomly assigned to the VR training group and non-VR training group by the study coordinator. A random allocation sequence will be generated in advance using a computerized random number generator by a biostatistician who will be not involved in this trial. The study coordinator who will be not involved in recruiting participants will keep the random list and will assign the treatment plans accordingly. The biostatistician and research coordinator will keep the random list until the end of the research to ensure that the assignment is blind to the participants and the attending physician who will recruit participants.

Although it is impossible to blind the participants and rehabilitation trainer due to this being a non-pharmacological intervention trial, the allocation will be blind to the outcome assessors and the data analyst. Participants will be instructed not to disclose the allocation to the attending physician and the outcome assessors.

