### Outcome measures

All participants in the study will be measured before the start of the study, after the intervention (3 weeks later), and again at a 6-month follow-up. A summary of all measurements in this trial is shown in Table 2.

**Table 2 Tab2:** Outcome domains and measurement instruments

Outcome domain	Measurement instrument	Abbreviation	T0	T1	T2

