### Statistical analysis

SPSS statistical software will be used to build and process all data collected. Paired *t* tests will be used to evaluate the differences between group rehabilitation metrics before and after rehabilitation training. An independent sample *t* test will be used for measurement data between the groups. *P* < 0.05 is considered as the standard for significant difference. In addition, covariance analysis will be performed to adjust for any significant demographic or clinical imbalances. A safety analysis is scheduled after randomization and active treatment of 18 patients. Exploratory subgroup analyses may be conducted. To prevent data loss, all questionnaires will be user-friendly and collected electronically, with all study personnel trained to identify and engage subjects most likely to drop out of subsequent evaluations.

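### The stated 80% power for TUGT is not shown to apply to the planned between-group t test

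*Protocol article*

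**What the plan says.** **Sample size calculation (protocol article).** The calculation rests on the primary outcome, TUGT. It states that "a sample of 28 participants (14 per group) would provide 80% power" "to detect a difference between group means of 3.16", with alpha 0.05. PASS is named as the program, and the calculation is described as one "which takes into account the number of sample groups and the number of evaluation measures". No SD, within-patient correlation, number of measures or named test is given. Recruitment is then set at 36 or more to allow for 20% dropout.

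**Outcome measures and Table 2.** Participants are "measured before the start of the study, after the intervention (3 weeks later), and again at a 6-month follow-up". TUGT is thus recorded once before treatment (T0) and twice after it (T1, T2).

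**Statistical analysis.** Paired t tests compare before with after. For the comparison of the arms, an independent-samples t "test will be used for measurement data between the groups". Covariance analysis is added only to adjust for significant demographic or clinical imbalances. No planned analysis combines the three TUGT measurements. The section does not say whether the independent t test uses final values or changes, or at which visit.

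**The concern.** A two-sample t-test calculation needs a difference, an SD, alpha, power and the allocation ratio. It does not use a number of measures. A repeated-measures calculation does, and its result also depends on the correlation between visits. The sample size section concerns one outcome, measured three times, so repeated evaluation of TUGT is the most natural meaning of the phrase.

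If that is what was done, the 80% refers to one estimand (for example a difference averaged over visits, or a group-by-time effect), while the trial would be decided by a t test that may target another. With only 28 evaluable patients there is little margin. A non-significant result would be hard to interpret if nobody can say what power the deciding test had.

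**Working it through.** **Inputs from the protocol article:** difference 3.16; 14 per group; power 80%; alpha 0.05 (two-sided assumed, since the article does not say); 1:1 allocation; visits T0, T1, T2. **Assumed, because not given:** the SD, and a within-patient correlation rho of 0.3 to 0.8, equal between all pairs of visits and with the same SD at each visit.

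**Step 1: the plan's own figure.** Without an SD, 14 per group cannot be reproduced forwards, so I solved for the SD. Power comes from the noncentral t distribution with 2n − 2 = 26 degrees of freedom and noncentrality 3.16 / (SD × √(2/14)). Power of 80% requires SD = 2.87, a standardised difference of 3.16/2.87 = 1.10. The dropout step does reproduce: 14/0.8 = 17.5, rounded up to 18 per group, or 36 in total. So 28 evaluable patients is compatible with an ordinary t test, provided the SD is about 2.87.

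**Step 2: suppose the basis was the mean of the two post-baseline visits.** The variance of that mean is SD² × (1 + rho)/2. For 14 per group to give 80%, SD × √((1 + rho)/2) must equal 2.87, which fixes the single-visit SD. The power of a t test at one visit with 14 per group follows:

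| rho | (1 + rho)/2 | single-visit SD | power, one visit | n per group for 80% |
|---|---|---|---|---|
| 0.3 | 0.65 | 3.56 | 62% | 21 |
| 0.5 | 0.75 | 3.32 | 68% | 19 |
| 0.8 | 0.90 | 3.03 | 76% | 16 |

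**Step 3: suppose the basis was a pre-post change (group by time over two visits).** The variance of a change is SD² × 2(1 − rho). Setting SD × √(2(1 − rho)) = 2.87 gives, for a t test on final values:

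| rho | 2(1 − rho) | single-visit SD | power, final values |
|---|---|---|---|
| 0.3 | 1.4 | 2.43 | 91% |
| 0.5 | 1.0 | 2.87 | 80% |
| 0.8 | 0.4 | 4.54 | 43% |

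A t test on change scores would keep the full 80% here, since with two time points it is the same test as the group-by-time test.

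**Step 4: sensitivity to the missing SD alone.** For a plain t test with 14 per group, power is 90% at SD 2.5, 77% at SD 3, 52% at SD 4 and 36% at SD 5.

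The planned test may therefore have more than, exactly, or much less than 80% power, depending on inputs the article does not state.

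**The case against.** The case against is substantial. The article never uses the term repeated measures. The clause about groups and measures follows the name of the program and may only describe what the software can do. The word measure also serves for instruments elsewhere in the article, so the phrase could mean outcomes rather than visits. The rest of the paragraph reads like an ordinary two-sample calculation, and Step 1 shows that the stated number fits one. An article also condenses a fuller protocol, and the PASS settings may be set out there.

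Much of this stands. A reader might infer that the sample size takes credit for repeated measurements and that the planned test is therefore underpowered. The document does not support that: the repeated-measures basis is an inference, and Step 3 shows that even the direction of any discrepancy is open. A reader might also average all three visits and obtain larger losses. That average would include T0, measured before treatment, where no treatment difference can be expected. Nor does the plan say that T2 is discarded; the between-group t test is not restricted to a visit.

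The mismatch in the text remains. Reading the phrase as a count of outcomes fits poorly with a calculation declared to rest on TUGT alone at an unadjusted alpha of 0.05. Reading the calculation as a plain t test means disregarding what the article itself says about it. The point is not merely that detail is absent: the article describes the basis of the calculation and names the tests, and the two do not correspond.

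**Conclusion.** The concern holds in a limited form: as described, the calculation and the analysis do not match, so the 80% cannot be attributed to the planned between-group test. A loss of power is possible but not demonstrated. On the assumptions above, the power of a single-visit t test with 14 per group is:

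- about 62–76% if the basis was the average of T1 and T2 (rho 0.3 to 0.8);
- about 91% (rho 0.3) to 43% (rho 0.8) if the basis was a pre-post change;
- 80% if the basis was a plain two-sided t test with SD about 2.87.

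The SDs and correlations are assumptions, not figures from the article. The point should be corrected before analysis, because the primary comparison rests on it.

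**What to change.** **Analysis.** Make the primary between-group analysis of TUGT time a pre-specified comparison at T1 adjusted for baseline TUGT, whether or not a baseline imbalance is significant. This can be an ANCOVA, or the T1 contrast of a mixed model for T1 and T2 with group, visit, group-by-visit and baseline TUGT. With complete data the two give nearly the same T1 contrast; the gain over the unadjusted t test comes mainly from the baseline adjustment.

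**Power statement.** Restate the power of 14 per group for that contrast, giving the assumed SD and baseline correlation and their source. Do not quote a repeated-measures power for a single-visit t test. Baseline adjustment reduces the SD to SD × √(1 − rho²). For illustration at rho 0.5, where √(1 − 0.25) = 0.866:

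- if the single-visit SD is 2.87, the adjusted SD is 2.87 × 0.866 = 2.49, and power is about 90%;
- if it is 3.32 (Step 2), the adjusted SD is 3.32 × 0.866 = 2.87, and power is about 80%.

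At rho 0.3 with the SD of 3.56 from Step 2, the adjusted SD is 3.56 × √(1 − 0.09) = 3.40 and power is only about 66%.

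**Cost.** A change to the analysis wording and one re-run in the software already named. T0, T1 and T2 data are already collected and no extra patients are needed. The downside is that the restated power may be less favourable than 80%.

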### Statistical analysis

SPSS statistical software will be used to build and process all data collected. Paired *t* tests will be used to evaluate the differences between group rehabilitation metrics before and after rehabilitation training. An independent sample *t* test will be used for measurement data between the groups. *P* < 0.05 is considered as the standard for significant difference. In addition, covariance analysis will be performed to adjust for any significant demographic or clinical imbalances. A safety analysis is scheduled after randomization and active treatment of 18 patients. Exploratory subgroup analyses may be conducted. To prevent data loss, all questionnaires will be user-friendly and collected electronically, with all study personnel trained to identify and engage subjects most likely to drop out of subsequent evaluations.

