### Participants

Inclusion criteria: (1) Aged 40–80 years. (2) Patients with ischemic cerebrovascular disease who met the classification and diagnosis criteria of cerebrovascular disease confirmed by head CT or MRI scan [23]. (3) The first ever stroke and initial stroke onset of 1 month or less. (4) Walking dysfunction (the standard of walking dysfunction in stroke patients was patients aged < 60 years with 10-m walking time ≥ 10s; patients aged 60–69 years with 10-m walking time ≥ 12.5 s; patients aged > 70 years with 10-m walking time ≥ 16.6 s). (5) The patient can stand with the help of one person or with crutches and can walk at least l0 m. (6) Lower limb muscle strength level of 3 or above.

Exclusion criteria: (1) Patients with serious behavioral problems or mental disorders. (2) Patients with cognitive impairment (MMSE ≤ 24 points) unable to cooperate with training. (3) Patients with cerebellar stroke, recent lower extremity deep vein thrombosis, quadriplegia, Parkinson’s disease, lower limb fractures, or recent myocardial infarction. (4) Patients with vital organ (heart, lung, liver, kidney, etc.) failure, malignant tumor, or other unstable condition. (5) Patients with history of cerebrovascular accident before this stroke and/or walking dysfunction. (6) Those who have previously completed routine gait training.

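### Within-arm paired t tests share one P < 0.05 standard with the between-group test, and the plan does not say which of them decides whether VR works

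*Protocol article*

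**What the plan says.** The Statistical analysis section of the protocol article names three analyses.

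- Paired t tests: "tests will be used to evaluate the differences between group rehabilitation metrics before and after rehabilitation training".
- An independent-samples t test: "test will be used for measurement data between the groups".
- ANCOVA, under a condition: "covariance analysis will be performed to adjust for any significant demographic or clinical imbalances".

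A single threshold follows for all of them: P "< 0.05 is considered as the standard for significant difference". The section does not name the analysis that decides efficacy and does not call the paired results descriptive.

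Three other sections bear on this. Under Participants, eligibility requires "The first ever stroke and initial stroke onset of 1 month or less". The intervention sections give both arms three weeks of gait training plus regular active exercise. The Sample size calculation is built on a contrast between arms: "a sample of 28 participants (14 per group) would provide 80% power" and "to detect a difference between group means of 3.16", on the TUGT.

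**The concern.** A paired t test on before–after data asks whether one arm changed. It cannot separate VR from whatever else moves both arms. Here two such influences are plausible: recovery in the weeks after a stroke, and the active training that the control arm also receives.

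A paired test can therefore be significant in the VR arm when VR adds nothing. Setting a significant VR arm beside a non-significant control arm is no valid substitute for comparing the arms, because the two P values can fall on either side of 0.05 by chance. With one threshold for both kinds of test and no deciding test named, the text leaves room for a conclusion on VR to be drawn from the wrong one.

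**Working it through.** **The plan's own figure.** The article gives no SD, so 14 per group cannot be reproduced independently. Solving backwards from 14 per group, 80% power, a difference of 3.16 and two-sided α = 0.05 (sidedness is assumed) gives an implied SD of 2.87 by the noncentral t. The dropout step does reproduce: 14/0.8 = 17.5, rounded up to 18 per arm, 36 in total. The 80% power belongs to the between-group test and cannot be carried over to the paired tests.

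**Inputs for the check.** From the article: two independent arms, 14 evaluable per arm (18 if nobody drops out), and threshold 0.05. Assumed: two-sided testing, no VR effect, and the same mean change μ and SD of change σ in both arms. The article gives neither μ nor σ, so the ratio μ/σ is varied.

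**Formulas.** The chance that one arm shows significant improvement is

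p = P(T > t critical value), where T is noncentral t with n − 1 degrees of freedom and noncentrality (μ/σ)√n.

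The arms are independent, so with no VR effect

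- P(VR arm significant, control arm not) = p(1 − p)
- P(at least one arm significant) = 1 − (1 − p)²

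The product p(1 − p) is largest at p = 0.5: 0.5 × 0.5 = 0.25. At p = 0.8 it is 0.8 × 0.2 = 0.16.

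**Results at n = 14 per arm, no VR effect**

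| μ/σ (assumed) | p, each arm | At least one arm | VR arm only |
|---|---|---|---|
| 0.25 | 14% | 26% | 12% |
| 0.5 | 41% | 65% | 24% |
| 0.75 | 74% | 93% | 19% |
| 1.0 | 93% | 99.5% | 6% |
| 1.1 | 97% | 99.9% | 3% |
| 1.5 | about 100% | about 100% | 0.1% |

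The row at 1.1 takes a common recovery of 3.16 and borrows the implied SD as the SD of change: 3.16/2.87 = 1.10. With 18 per arm and μ/σ = 0.5, p is 52% and the VR-only figure is 25%.

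**Between-arm test on the same data.** In 200,000 simulated trials at n = 14 with no VR effect, the independent t test on change rejected in 5.0%, 5.0% and 4.9% of trials at μ/σ = 0.5, 0.75 and 1.1. It holds its nominal level whatever the common recovery. Half of 5%, or 2.5%, would falsely favour VR.

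**The case against.** The strongest reply is that the valid comparison is already there. The independent t test comes directly after the paired tests, ANCOVA is available, the sample size rests on a difference between arms, and the Discussion describes a comparative evaluation in a randomized experiment. Nowhere does the article say that a paired result will count as evidence for VR. All of this stands. The percentages above become false-claim rates only if someone uses the paired pattern to decide. The comparison with 2.5% is subject to the same condition.

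Three stronger readings are tempting, and the documents do not support them.

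- A reader might infer that natural recovery will make an arm significant whatever VR does. The article gives no recovery size and no SD of change, and over the assumed range the chance per arm runs from 14% to about 100%. The supportable word is can.
- A reader might take 25% as the expected risk. It is the maximum of p(1 − p). When recovery is strong enough to make each arm significant almost every time, the VR-only pattern becomes rare.
- A reader might conclude that a within-arm test is being passed off as a between-group test. The phrase is more likely awkward English for each group's metrics before and after training, which is the only reading that a paired test fits.

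It can also be said that a condensed article may leave the choice of deciding test to an analysis plan that is not shown. That lowers the weight of the point but does not remove it. The article does state two kinds of test under one significance standard, and it limits baseline adjustment to significant imbalances.

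**Conclusion.** The point holds as a needed clarification. The plan has a valid test and is sized for it, but it places within-arm tests beside it at the same threshold without giving the valid one precedence. If the paired results were used as evidence for VR, trials with no VR effect would show the misleading pattern in at most 25% of cases, in 16% at 80% power per arm, and in about 3–6% when μ/σ is 1.0 to 1.1. In that last range the remaining hazard is different: the VR arm is significant in 93–97% of null trials, which says nothing about VR. These figures assume equal true change in both arms, roughly normal changes, 14 per arm and two-sided 0.05. The recovery size is an assumption throughout.

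**What to change.** In the Statistical analysis section:

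1. Report before–after change within each arm as a mean with 95% CI, for description only, with no test of effect attached.
2. State that any conclusion on VR rests on the between-arm comparison of TUGT.
3. Make that comparison an ANCOVA adjusted for baseline TUGT in every case, and not only when an imbalance turns out significant. Baseline TUGT is already scheduled for all participants in Table 2, and adjusting for it generally improves precision over an unadjusted t test.

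Items 1 and 2 are wording. Item 3 is a small change to the analysis, because it replaces a conditional adjustment with a fixed one. No new data or patients are needed.

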### Safety

VR is an emerging technology and its related products have been gradually developed in recent years. To date, no relevant adverse events have been reported. In the process of training subjects’ gait recovery with VR technology; our research team will strictly follow the relevant regulations of the medical ethics committee to ensure the maximum safety and ethical protection of subjects. As VR technology is a relatively new technology, subjects may not be able to complete training tasks due to ineptness or intolerance (such as dizziness, nausea, sore eyes, disorientation) during training. Adverse events (e.g., falls, pain, and dizziness) that occur during the study period, whether or not related to the study intervention are registered. Considering the above two aspects, we will take the following measures to achieve the best training environment:
During the 3-week training, a strict training plan will be made for each subject on a weekly basis, adjusting the training schedule according to the actual conditions of the subjects;Pay close attention to the feedback and fitness of subjects using VR technology for rehabilitation training;Periodically evaluate the intervention effect of subjects using VR technology for rehabilitation training; andSupporting subjects’ decision to withdraw from the study.

This study will strictly comply with the requirements of clinical operation guidelines and internationally recognized legal requirements. Any adverse events will be reported directly to the ethics committee immediately, and the training regimen will be adjusted accordingly after each adverse event. There is no anticipated harm and compensation for trial participation.

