VR technology leverages interactive simulations to create an environment that is similar to the real-world scenarios. Stroke patients can complete tasks as required and interact with virtual objects. Previous studies have pointed out that such human-computer interactions should be easy to adapt, be intuitive and convenient to use, and allow the subjects to readily transfer the skills learned in the virtual environment to real life. In addition, VR can provide immediate motor feedback during training, allowing for task-oriented repetitive exercises while enabling changes to the traditional treatment patterns which can feel repetitive or boring for patients. In the form of a virtual game, the treatment of patients with lively and interesting scenes and training projects allows patients to feel more relaxed, engaged, and therefore more invested in the active participation. The real-time feedback can additionally provide patients with a greater awareness of their training and performance [37]. In addition to repetitive training, the modulation of different environments during a VR-assisted training session can also be very helpful for patients’ learning ability, which can enhance the ability of patients to adapt to the environment and thus improve their sports learning ability [3, 38]. This mode of higher participation can ultimately improve the enthusiasm and acceptance of training for patients, reducing the dropout rate and enabling patients to maintain long-term rehabilitation [39]. Moreover, studies have shown that immersive VR is feasible in the rehabilitation of stroke patients with gait disorder [20]. Interestingly, one study has found that subjects receiving occasional intermittent treatment were more effectively impacted than others receiving daily treatment [40].

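### The named between-group t test sets aside recorded TUGT values, and its 6-month contrast is biased if walking-related loss differs between the arms; a repeated-measures model is a cheap improvement

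*Protocol article*

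**What the plan says.** All references are to the protocol article.

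- **Statistical analysis, main comparison.** Between groups, an independent-sample t "test will be used for measurement data between the groups". Paired t tests cover before-to-after change, and P < "0.05 is considered as the standard for significant difference". No visit, analysis set or sidedness is attached to the between-group test.
- **Statistical analysis, adjustment.** In addition, "covariance analysis will be performed to adjust for any significant demographic or clinical imbalances". Adjustment therefore depends on an imbalance being found, and baseline TUGT is not named as a covariate.
- **Statistical analysis, missing data.** The measures are preventive: "To prevent data loss, all questionnaires will be user-friendly and collected electronically", and staff are trained to spot and engage patients likely to miss later evaluations.
- **Outcome measures and Table 2.** TUGT, the only primary outcome, is taken at T0, T1 and T2.
- **Sample size calculation.** 28 evaluable patients (14 per group) "would provide 80% power" for a difference of 3.16. The target becomes 36, "allowing a dropout rate of 20"%.
- **Discussion.** The engaging form of VR training is credited with "reducing the dropout rate and enabling patients to maintain long-term rehabilitation".
- **Safety.** With VR, "subjects may not be able to complete training tasks due to ineptness or intolerance", for example because of dizziness or nausea.

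**The concern.** A two-sample t test of T2 TUGT compares only the patients measured at T2. For a patient lost between T1 and T2, the two values already recorded contribute nothing. For patients who return, their own earlier values are not used either.

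This is harmless for bias if the patients who leave are selected in the same way in both arms. It is not harmless if the arms lose different kinds of patients, or the same kind at different rates. The protocol gives reasons to think this possible: lower dropout under VR-style training on one side, VR intolerance on the other. The T2 difference would then partly reflect who stayed. The T1 value that could correct for much of this is collected but plays no part in the named test.

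The point concerns the test that the protocol names. That the article has no missing-data section is not a finding, since a full protocol or SAP may contain one.

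**Working it through.** **1. The plan's own figures.** 14/(1 − 0.20) = 17.5, so 18 per arm and 36 in total, as stated. The 28 cannot be derived forward because no SD is given. Solving a two-sided 5% t test with 14 per arm, 80% power and a difference of 3.16 gives SD = 2.87. A one-sided test would imply 3.27. I use 2.87 and read TUGT in seconds.

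**2. Assumptions not in the documents.** T1 and T2 are bivariate normal with correlation ρ from 0.5 to 0.9. Loss occurs after T1, is logistic in T1 with slope 1 (moderate) or 2 (steep) per SD, and is 20% overall.

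**3. Formula.** Let δ be the mean standardised T1 among patients who stay in an arm. With no true effect, the t test's bias is

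bias = ρ × SD × (δ_VR − δ_control).

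If slow walkers tend to leave, numerical integration gives δ = −0.091, −0.173 and −0.253 for 10%, 20% and 30% loss at slope 1. At slope 2 the values are −0.143, −0.262 and −0.375.

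**4. Same selection in both arms.** δ_VR = δ_control, so the bias is 0. Simulation agrees: at most about 0.01 s in 20,000 trials of 18 per arm, with a false-positive rate of about 5%.

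**5. Selection in one arm only (20% loss in each).** At slope 1 and ρ = 0.7: 0.7 × 2.87 × 0.173 = 0.35 s. Slow walkers leaving VR only would favour VR.

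**6. Unequal loss, 10% VR and 30% control, same slope.** At slope 1 and ρ = 0.7: 0.7 × 2.87 × (−0.091 + 0.253) = 0.33 s, against VR.

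| Scenario | Slope | Absolute bias, ρ 0.5 / 0.7 / 0.9 (s) | Simulated false-positive rate |
|---|---|---|---|
| One arm only | 1 | 0.25 / 0.35 / 0.45 | 5.6% to 7.1% |
| 10%/30% loss | 1 | 0.23 / 0.33 / 0.42 | 5.5% to 6.4% |
| One arm only | 2 | 0.38 / 0.53 / 0.68 | 6.3% to 9.6% |
| 10%/30% loss | 2 | 0.33 / 0.47 / 0.60 | 6.1% to 9.0% |
| Opposite in the two arms | 1 | 0.50 / 0.70 / 0.90 | 7.4% to 13.3% |
| Opposite in the two arms | 2 | 0.75 / 1.05 / 1.35 | 10.9% to 27.0% |

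With 15%/25% loss at slope 1 the bias is only 0.12 to 0.21 s.

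**7. A true VR effect on T1.** If VR improves TUGT by 3.16 at T1 and T2, and both arms share one loss function of T1, large simulations with ρ 0.5 to 0.85 gave a bias of 0.17 to 0.62 s against VR. With one shared loss function of T0 the bias was about 0.

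**8. Alternatives.** An estimator that uses the earlier TUGT values stayed within 0.03 s of zero in every one of these settings. ANCOVA on T0 among patients with T2 removed the bias when loss depended on T0 only. It left 0.03 to 0.18 s when loss depended on T1 and differed between arms.

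**9. Precision under random loss.** The standard error ratio is approximately √(1 − 0.20 × ρ²), which is 0.975, 0.950 and 0.915 for ρ = 0.5, 0.7 and 0.9. That is about 3% to 9% smaller.

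**The case against.** **Same selection cancels.** A reader might infer that the T2 contrast is biased whenever loss depends on earlier walking. Step 4 shows that this is wrong: loss must differ between arms, or follow a T1 that VR has shifted.

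**Evidence for differential loss is thin.** The Discussion sentence is a general remark about VR-style participation and gives no rates for this trial. The Safety sentence is about finishing tasks during the 3-week programme, not about attending at 6 months. This stands: differential loss is foreseeable, not established. The largest figures in the table need opposite selection in the two arms, which the documents nowhere state, so they should not be taken as the expected size.

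**The protocol has other protections.** Staff training to engage likely dropouts covers all evaluations, TUGT included, so it would be wrong to call electronic questionnaires the only safeguard. The covariance analysis could help too. But retention measures reduce loss without correcting for what remains, and the covariance analysis depends on a significant imbalance and does not name TUGT.

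**The analysis set is not stated.** A reader might infer a per-visit test on whoever is still present, or, from Quality control and quality assurance, an analysis restricted to training completers. The first section names no visit or set. The second speaks of checking completers' data for completeness and quality, and does not define the set for TUGT. What does follow is narrower: a t test of T2 values needs T2 values.

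**The model is not a full cure.** Patients who stop because of VR intolerance may leave before T1. With all loss placed before T1 but driven by T1-level walking, the proposed type of estimator kept a bias of 0.06 to 0.13 s (one arm, slope 1) and 0.16 to 0.40 s (opposite selection, slope 2). That is less than the t test's bias, but not zero.

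**Conclusion.** The point holds in a limited form. The named t test is a weak choice for a primary outcome recorded three times with 20% loss budgeted. Its T2 contrast is biased if walking-related loss differs between arms in rate or pattern, or follows a T1 value changed by VR, and it is unbiased if selection is equal.

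Under moderate dependence on T1, with selection in one arm or 10%/30% loss, the bias is about 0.2 to 0.5 s, or 7% to 14% of 3.16 (0.23/3.16 and 0.45/3.16). The false-positive rate is about 5% to 7%. Steep dependence raises this to about 0.3 to 0.7 s and 6% to 10%.

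These sizes rest on a back-solved SD and on assumed correlation and loss models. Bias is proportional to SD, so an SD of 3.27 multiplies it by 3.27/2.87 = 1.14. The direction can favour either arm. This is a cheap improvement, not a defect that invalidates the trial.

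**What to change.** In Statistical analysis, make the TUGT between-group comparison a likelihood-based repeated-measures model:

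- all randomised patients with any T0, T1 or T2 TUGT value, in their allocated arm;
- arm-by-visit means with a common baseline mean;
- unstructured covariance across the three visits;
- the arm difference reported at T1 and at T2.

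Keep the independent-sample t test on observed cases as a sensitivity analysis.

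The cost is a change of wording and slightly more analysis work, with no new patients, visits or measurements. The model relies on loss being explained by the recorded TUGT values. This is a weaker assumption than loss unrelated to walking, but it can fail, above all for patients who leave before T1. The number lost before T1 and between T1 and T2 should therefore be reported by arm.
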